**Pain and disability**	
Oswestry Disability Index, change from baseline to 3- and 12-month follow-up Roland Morris disability questionnaire, change from baseline to 12-month follow-up	
PROMIS (Patient-Reported Outcomes Measurement Information System) (short form 20a), change from baseline to 3-month follow-up	
Frequency of LBP during last 3 months, change from baseline to 3- and 12-month follow-ups	
LBP intensity (0–10 numerical rating scale (NRS)) during last week, change from baseline to 3- and 12-month follow-ups	
Leg pain intensity (NRS) during last week change from baseline to 3- and 12-month follow-ups	
SBT (STarT Back Tool) change from baseline to 12-month follow-up	
**Health-related quality of life**	
EQ-5D (EuroQol five dimensions) change from baseline to 12-month follow-up	
**Direct costs**	
Physician visits during last year	
Physiotherapist visits during last year	
Nurse visits during last year	
Other health care professional visits (e.g. psychologist) during last year	
Imaging due to LBP (x-ray/MRI/CT) during last year	
Pain medication during first year	
Back surgery rate	
**Indirect costs**	
Days on sick leave during last year (LBP-related and all sick leaves)	
Disability pensions during first year	

### Participant timeline

The baseline evaluation of the health care regions will contain organizational data, professional data, and patient-level data (described later). Approximately 1 year after baseline evaluation, we will implement a classification-based biopsychosocial model for the LBP patients in the study’s health care regions (Fig. 2). After implementation, the health care regions will be re-evaluated in a similar manner to that at baseline. In each region, data before the implementation will be compared to data after the implementation.

**Fig. 2 Fig2:**
[figure not shown]
Flow chart of intervention

### Sample size

The primary outcome measure for this trial is the change in PROMIS from baseline to 12-month follow-up. Our sample size calculation is based on the following hypothesis test: superiority of a classification-based approach to LBP in primary care compared to best current care. For sample size calculation, we will use G*Power 3.1. (Difference between two dependent means). The Minimal Important Difference (MID) for PROMIS PF-20 change is about 2 points, Standard Deviation (SD) is 3.66 [48]. The effect size is 0.5, and type I error rate 0.05. A sample size of 34 patients per group (health care region) would enable the detection of a difference of 2 points in PROMIS with 80% power. With a 40% drop-out rate and 6 groups (3 before and 3 after), the final sample size is 340 patients.

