### Recruitment

All GPs and PTs in the study health care centres will be invited to participate in the study. In all the centres, the clinicians (nurse, PT or physician) will receive 30 min of training on the study and eligibility criteria. After this, they will identify patients when consulted for LBP*.* The clinician will inform the identified patient of the study, give them patient information and ask for their consent. In most cases, the first contact and recruiting clinician is a nurse or PT, even if the patient also has a physician appointment, and this should reduce selection bias. Signed consent forms will be sent to the research nurse (out of clinic). The physicians and PTs will be informed and reminded monthly about the study via email. We will use the same recruiting strategy before and after the implementation of the classification-based approach.

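### The sample size uses a paired-means formula for a comparison of different patients before and after implementation, so 34 per group gives about 53–60% power in each region, not 80%

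*Protocol article*

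**What the plan says.** The protocol's Sample size section fixes these elements:

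- Endpoint: "The primary outcome measure for this trial is the change in PROMIS from baseline to 12-month follow-up".
- Hypothesis: "superiority of a classification-based approach to LBP in primary care compared to best current care".
- Method: "For sample size calculation, we will use G*Power 3.1. (Difference between two dependent means".
- Inputs: "The Minimal Important Difference (MID) for PROMIS PF-20 change is about 2 points, Standard Deviation (SD) is 3.66 [48", and "The effect size is 0.5, and type I error rate 0.05".
- Result: 34 patients per group, the group being a health care region, which "would enable the detection of a difference of 2 points in PROMIS with 80% power".
- Total: "With a 40% drop-out rate and 6 groups (3 before and 3 after), the final sample size is 340 patients".

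The Participant timeline section says that before and after data will be compared within each region. The Recruitment section says that patients are enrolled in both periods: "We will use the same recruiting strategy before and after the implementation of the classification-based approach". No section describes matching or pairing a patient in one period with a patient in the other.

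**The concern.** A dependent-means test needs two measurements on the same unit. Here the only pairing is each patient's own baseline and 12-month scores, and the primary endpoint has already turned that pair into one change score. Superiority over current care is then a comparison of mean change between two sets of different people. The count of six groups, three before and three after, confirms this: if the same patients served in both periods there would be three groups.

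A paired test in a single group of 34 asks whether those patients changed over a year. Back pain patients may change under either form of care, so that question does not test whether care improved. If the formula is wrong for the hypothesis, the stated 80% power is wrong too. The regional comparisons that the protocol plans would then miss a true 2-point benefit far more often than one time in five.

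**Working it through.** **Inputs, all from the Sample size section:** difference 2 points; SD 3.66; stated effect size 0.5 (2/3.66 = 0.546, so 0.5 is a rounding down); type I error 0.05; 34 per group; six groups; 40% loss. Sidedness is not stated.

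**1. Reproduce the plan's figure.** For a paired t-test, the noncentrality is d√n with n − 1 degrees of freedom.

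- d = 0.5, two-sided, n = 34: 0.5 × √34 = 2.915 on 33 df gives power 80.8%. With n = 33, power is 79.5%. So 34 is the smallest n that reaches 80%.
- Total: 6 × 34 / (1 − 0.40) = 204 / 0.6 = 340.

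Both figures reproduce exactly. The other paired variants do not give 34: one-sided d = 0.5 needs 27, two-sided d = 0.546 needs 29, and one-sided d = 0.546 needs 23. The plan therefore used the two-sided paired test at d = 0.5.

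**2. Power for the comparison that tests the hypothesis.** For two independent groups of n, the noncentrality is d√(n/2) with 2n − 2 degrees of freedom. With n = 34 (66 df), two-sided:

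| Effect size | Noncentrality | Power |
|---|---|---|
| 0.5 (as stated) | 0.5 × √17 = 2.062 | 52.9% |
| 0.546 (2/3.66) | 0.546 × √17 = 2.253 | 60.3% |

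One-sided testing at 0.05 gives 65.4% and 72.1%, still below 80%.

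**3. Detectable difference.** With 34 versus 34, 80% power needs d = 0.690. In points this is 0.690 × 3.66 = 2.52.

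**4. Size needed for 80% power in each region (two-sided).**

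| Effect size | Completers per group | Completers, six groups | Enrolled at 40% loss |
|---|---|---|---|
| 0.5 | 64 | 384 | 384 / 0.6 = 640 |
| 0.546 | 54 | 324 | 324 / 0.6 = 540 |

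**5. Pooled comparison at the planned size.** 340 × 0.6 = 204 completers, or 102 per period. The noncentrality is 0.5 × √51 = 3.571 or 0.546 × √51 = 3.902, which gives power of 94.5% or 97.3%.

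**6. Illustration of clustering.** The plan makes no allowance for patients sharing centres and clinicians, and gives no intraclass correlation. The design effects here are assumptions; each divides n.

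| Assumed design effect | Per region, d = 0.5 / 0.546 | Pooled, d = 0.5 / 0.546 |
|---|---|---|
| 1.1 | 49.0% / 56.1% | 92.3% / 95.9% |
| 1.5 | 37.7% / 43.6% | 82.5% / 88.6% |

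As a guide to scale, Rovaniemi has four centres. If they recruit equally, that is 34 / 4 = 8.5 completers each, and an assumed intraclass correlation of 0.02–0.05 gives 1 + 7.5 × 0.02 = 1.15 to 1 + 7.5 × 0.05 = 1.38. In a before–after comparison within the same centres, only the centre-by-period part of the variation inflates the variance.

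**The case against.** The strongest reply is that the study is not too small for its main question. The hypothesis sentence names no region, and the same 340 patients give 94–97% power when pooled. This stands in part: the enrolment target can be kept. It does not rescue the text, because the 80% is attached to a group defined as a region, the Participant timeline section plans the comparison within each region, and no pooled analysis is named as the basis for sizing.

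A second objection is that 3.66 is not expressly labelled as the SD of change. If it were the SD at a single time point, the change SD would be 3.66√(2(1 − r)). At assumed baseline-to-12-month correlations r of 0.3, 0.5, 0.7 and 0.8, power for 2 points at 34 versus 34 would be 47%, 60%, 82% and 94%. So the 60.3% and the 2.52 points are conditional on reading 3.66 as the SD of change. That is the natural reading, since the figure stands beside an important difference for change and 2/3.66 is close to the stated effect size. The 52.9% needs no SD, as it follows from the plan's own effect size of 0.5.

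Third, the clustering figures rest on assumed values, and a design effect of 1.5 lies above the 1.15–1.38 worked out for Rovaniemi. This is fair: they are illustrative, and the conclusion does not depend on them.

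Fourth, the Discussion says unsuccessful implementation will be judged from organizational, professional and patient data together, so a null PROMIS result alone need not be read as failure. This is also fair. The risk of misreading is reduced, but the power statement remains wrong.

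**Conclusion.** The concern holds. The plan's arithmetic is correct for the test it names, but that test does not address the stated hypothesis. For the independent before–after comparison in a region, 34 completers per period give 53–60% power with a two-sided test at 0.05, so a true effect of the planned size would be missed 40–47% of the time instead of 20%. The 53% uses the stated effect size of 0.5. The 60%, and the detectable difference of 2.52 points, take 3.66 as the SD of change. All of these figures ignore clustering, which would lower them. Pooled over the three regions, the planned enrolment gives 94–97% power, or 82–96% under assumed design effects of 1.1–1.5. The error therefore lies in the justification and in the regional power claim. It must be corrected, because the plan states a power that the design does not deliver for its primary hypothesis.

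**What to change.** Keep 340 patients and rewrite the Sample size paragraph:

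1. Replace the dependent-means calculation with one for two independent means, and state that the test is two-sided and that 3.66 is the SD of the change score, if it is.
2. Attach the powered claim to the before–after comparison pooled over regions: 102 versus 102 completers, about 94–97% power before clustering, shown over a plausible range of design effects.
3. State that 34 completers per region and period give 53–60% power for the planned effect, so regional estimates are descriptive and reported with confidence intervals.

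This needs no extra patients. The price is a weaker claim for single regions. The Participant timeline and Discussion sections need a matching sentence, since both speak of before–after comparison within each region. Implementation conditions differ between regions (Table 3), so the regional estimates should be shown beside the pooled one. If the sponsor wants each region to be conclusive on its own, the alternative is 540–640 enrolled patients, before any allowance for clustering.

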### Recruitment

All GPs and PTs in the study health care centres will be invited to participate in the study. In all the centres, the clinicians (nurse, PT or physician) will receive 30 min of training on the study and eligibility criteria. After this, they will identify patients when consulted for LBP*.* The clinician will inform the identified patient of the study, give them patient information and ask for their consent. In most cases, the first contact and recruiting clinician is a nurse or PT, even if the patient also has a physician appointment, and this should reduce selection bias. Signed consent forms will be sent to the research nurse (out of clinic). The physicians and PTs will be informed and reminded monthly about the study via email. We will use the same recruiting strategy before and after the implementation of the classification-based approach.

### Data collection, management and analyses

We will collect organizational data, professional data and patient-level data (Table 5). Organizational administrative register data will be collected directly from each health care organization and will contain no identifiable patient information. The first professional data collection will be conducted after the professionals have undergone a 15–30-min study information session. The research nurse will send a web-based questionnaire to all the physicians and PTs in the study health care units who have consented to participate in the study (Table 6). Professional data will be collected from each health care unit and will contain no identifiable individual practitioner data.

**Table 5 Tab5:** Evaluation of health care region

Domain	Measures
**Organizational**	Number of physician appointments according to ICD10 M40-M53
	Imaging examinations
	Secondary care consultations due to LBP
**Professional**	Professionals’ beliefs and attitudes to LBP
**Effectiveness of LBP care**	Patient data (outcomes described in Table 6)
**Cost-effectiveness**	Direct costs
	Indirect costs

**Table 6 Tab6:** Components of professional data collection

Domain	Measures
**Descriptive data**	Gender
	Occupation (physician/physiotherapist/occupational nurse/other)
	Clinical work experience
	Health care unit for work
	Proportion of patients with LBP of all consultations
**Attitudes and beliefs**	Back pain beliefs questionnaire
	ABS-mp (Attitudes to Back Pain Scale, for musculoskeletal practitioners)
**Routines and satisfaction**	Use of patient education leaflet
	Use of risk stratification tool in practice (e.g. SBT)
	Satisfaction with treatment
	Level of confidence in own skills

Patient- level data will be collected through baseline and follow-up surveys at 3 months and 1 year via web-based questionnaires. The research nurse will email the patients the baseline questionnaire link after receiving their signed consent. We will aim to have the responses to the baseline questionnaires between one and 3 weeks after the consultation in the research health care unit. If an email address is missing, the research nurse will call the patient to acquire it or send them a paper version of the questionnaire. The research nurse will resend the link 1 week later if no response is received. After 2 weeks, and again after 3 weeks, the research nurse will remind the patients who have not answered and will send them a text message with a hyperlink to the questionnaire. The patients’ questionnaire includes descriptive data and the validated symptom-related questions listed in Table 7.

**Table 7 Tab7:** Components of patient-level data collection

Domain	Measures	Time Point (months)
**Descriptive data**	Age and gender	0
	Occupation	0
	Weight and height	0
	Country of birth	0
	Pregnancy	3, 12
**Lifestyle**	Leisure time physical activity	0
	Smoking	0, 12
**Comorbidity**	Diabetes, rheumatoid arthritis, ankylosing spondylitis, osteoarthritis, depression, fibromyalgia, inflammatory bowel disease, muscle disease	0
**Back pain**	Previous back pain episode of at least two weeks’ duration	0
	Previous (lifetime) physician consultations related to back pain	0
	Frequency of LBP during last three months	0, 3, 12
	LBP intensity during last week, using 0–10 scale NRS (Numeral Rating Scale)	0, 3, 12
	Leg pain intensity during last week, using 0–10 NRS	0, 3, 12
**Work status**	Employment/unemployment/pension/student/unpaid work at home/other	0
	LBP-related sick leave during last three months	0, 3
	LBP-related sick leave during last nine months	12
	LBP-related part-time sick leave during last three months	0, 3
	LBP-related part-time sick leave during last nine months	12
	Work modifications due to LBP	0, 3, 12
**Use of health care resources**	Physician consultations during last three months	0,3
	Physician consultations during last year	12
	Physiotherapist consultations during last three months	0,3
	Physiotherapist consultations during last year	12
	Nurse consultations during last three months	0,3
	Nurse consultations during last year	12
	Other health care clinician consultation (e.g. psychologist, occupational therapist) during last three months	0,3
	Other health care clinician consultation (e.g. psychologist, occupational therapist) during last year	12
	Imaging due to LBP (x-ray/MRI /CT) during last year	0, 12
	Imaging due to back pain (x-ray/magnetic resonance imaging/computed tomography) during last three months	3
	Referral for imaging examinations (x-ray/MRI/CT) due to back pain	0, 3, 12
**Medication**	Over-the-counter pain medication during last week	0, 3,12
	Prescription pain medication (paracetamol/anti-inflammatory/mild opioid/strong opioid/others)	0, 3, 12
**Surgery**	Spine operation	12
**Patient satisfaction**	With information related to pain explanation	0, 3, 12
	With self-efficacy	0, 3, 12
	With health care provider’s skills	0, 3, 12
	With being heard and understood in terms of symptoms	0, 3, 12
**Pain and disability**	PROMIS PF-20 (Patient-Reported Outcomes Measurement Information System, 20-item physical functioning short form)	0, 3, 12
	STarT Back Tool	0, 12
	Örebro Musculoskeletal Pain Screening Questionnaire	0
	Oswestry Disability Index	0, 3, 12
	Roland Morris Disability Questionnaire	0, 12
**Beliefs**	FABQ (Fear avoidance Beliefs Questionnaire)	0, 12
	PSEQ (Pain Self-Efficacy Questionnaire)	0, 12
	BBQ (Back Beliefs Questionnaire)	0, 3
**Depressive symptoms**	DEPS (Depression Scale)	0
**Work ability**	Current work ability compared with lifetime best (0–10)	0, 3, 12
	Work ability in relation to demands of job	0, 12
	Estimated work impairment due to disease	0, 12
	Own prognosis of work ability two years from now	0, 12
**Health-related quality of life**	EQ 5D (EuroQol five dimensions)	0, 3, 12

*MRI* magnetic resonance imaging, *CT* computed tomography

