## Background

Guidelines recommend biopsychosocial frameworks for low back pain (LBP) management and avoidance of inappropriate imaging [1–3]. In clinical practice, care strategies are not always aligned with evidence and guidelines even though LBP is the most common disabling health condition worldwide [4, 5]. Unhelpful beliefs, attitudes and inappropriate imaging are common [6, 7]. A specific cause of pain can only be found for a small percentage of LBP patients, and over 90% are classified as having non-specific pain [8]. LBP is a complex condition in which biological, psychological, and social factors impact on both the experience of back pain and the associated disability [3, 9]. Risk factors for poor prognosis of LBP include high pain intensity, adverse subjective belief of long-lasting pain, low self-efficacy (i.e. confidence in one’s own ability to get on with life despite the pain), passive coping strategies, high catastrophizing and fear avoidance beliefs, depression, sleep problems, psychological distress, low education and social class, and unemployment [3, 4, 10–12].

In addition to patient-related factors and management, professional and health care system-related factors also affect the outcomes of patients with LBP. Such factors include imaging policy, patient education, the attitudes and beliefs of health care professionals, and the timing of rehabilitation [2, 13, 14].

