### Eligibility criteria

All patients aged 18–65 who contact health care due to LBP, either with or without radicular pain, will be included in the study. Exclusion criteria are: 1) Age under 18 or over 65; 2) First patient-reported contact with health care due to LBP and episode lasting less than 2 weeks; 3) Suspicion of a serious cause of LBP or LBP requiring urgent care. Patients will receive written information on the study. Only patients who sign the consent form will be included in the study.

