**Fig. 1 Fig1:**
[figure not shown]
Aim of care pathway

**Table 3 Tab3:** Health care region-specific challenges and strengths during implementation process

Health care region	Challenges	Strengths
ESSOTE	A simultaneous extensive organizational change (fusion of primary and secondary health care organizations, including relocation of primary care facilities)	Research nurses and the principal investigator can remind/educate professionals of the new protocol from time to time. During the re-evaluation, additional education lessons will take place in units during • emergency duty nurses’ meeting 2x60min • student health care unit nurses’ meeting 1x90min • junior physicians’ meeting 1x75min • GPs’ meeting 1x60min • general medicine department nurses’ meeting 2x30min • PTs’ meeting 2x30min • occupational health physicians’ meeting • PTs’ meeting 1x60min The nurse in charge of the emergency room is active in improving the implementation of the new care strategy.
Rovaniemi	Low GP participation rate in education. Emergency department not part of the study. Simultaneous relocation of primary health care facilities. No occupational health service organization included the study.	Previously complicated wide criteria for direct access to PT enormously reduces the possibility to use it. A notable criterion for direct access to physiotherapy during implementation process might be helpful.
EKSOTE	Simultaneous change in electronic medical record system increases requirements to adopt new working practices among professionals.	Some biopsychosocial oriented education for PTs had been held before this study, which is helpful for implementation. Mentoring will be arranged for PTs during implementation and re-evaluation.

ESSOTE (Etelä-Savon sosiaali- ja terveystoimi, The South Savo social and health care authority), EKSOTE (Etelä-Karjalan sosiaali- ja terveyspiiri, South Karelia social and health care district)

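### The regional appointment count in Table 5 uses ICD-10 M40-M53, which leaves out M54, the category for low back pain and sciatica

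*Protocol article*

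**What the plan says.** Under Data collection, management and analyses, the protocol article states that "Organizational administrative register data will be collected directly from each health care organization", without identifiable patient information. Table 5 lists three organisational measures: physician appointments, imaging examinations and secondary care consultations. Only the first has a diagnosis code: "Number of physician appointments according to ICD10 M40-M53". The third is described by condition: "Secondary care consultations due to LBP". No other ICD code or range appears in the article.

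The condition studied is set out elsewhere. Eligibility criteria takes in patients aged 18 to 65 who "contact health care due to LBP, either with or without radicular pain". The Background says that a specific cause is found in only a small percentage of LBP patients and that "over 90% are classified as having non-specific pain".

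On use of the data, Participant timeline says: "In each region, data before the implementation will be compared to data after the implementation". The Discussion adds that organisational, professional and patient-level data will be combined to identify best practice or unsuccessful implementation. Table 3 records, as a challenge for EKSOTE during implementation: "Simultaneous change in electronic medical record system increases requirements to adopt new working practices among professionals".

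**The concern.** The row sits in a table meant to evaluate LBP care in each region, so a reader will take it as the number of physician appointments for LBP. In ICD-10, the dorsopathies block runs from M40 to M54, and M54 is its last category. M54 is dorsalgia, which includes low back pain, sciatica and lumbago with sciatica. A range that ends at M53 keeps the deformities, spondylopathies, disc disorders and other dorsopathies, including cervical disc disorders (M50). It drops the symptom category a clinician would naturally use for LBP without a specific cause.

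What is at stake is the before-after appointment comparison in each region and its contribution to the judgement on implementation. Whoever extracts the register data will follow the printed range.

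**Working it through.** The plan states no figure that depends on this range, so there is nothing to reproduce. The check is a comparison of definitions, followed by arithmetic on assumed values.

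**Definitions side by side**

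| Item | Where | Content |
|---|---|---|
| Codes counted | Table 5 | M40 to M53 |
| Code left out | ICD-10 title | M54 dorsalgia: low back pain, sciatica, lumbago with sciatica |
| Population | Eligibility criteria | LBP with or without radicular pain |
| Typical case | Background | more than 90% non-specific |
| Neighbouring measure | Table 5 | secondary care consultations for LBP |

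The population and the neighbouring measure are defined by LBP. The appointment count is defined by a range that excludes the category named for it.

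**Size of the omission**

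Let s be the share of LBP appointments coded M54. The M40-M53 range misses exactly s of them. The article does not give s. As an assumption only:

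| Assumed s | LBP appointments missed |
|---|---|
| 30% | 30% |
| 50% | 50% |
| 70% | 70% |
| 90% | 90% |

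To see what it would take for more than half to be missed, suppose that 90% of appointments, like 90% of patients, are non-specific and that M54 is used only for these. Then s = 0.90 × p, where p is the share of non-specific appointments coded M54. Setting s > 0.50 gives p > 0.50 / 0.90 = 0.556, about 56%. The article says nothing about p.

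**Effect on the before-after comparison**

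Let N1 and N2 be the true numbers of LBP appointments before and after, and s1 and s2 the M54 shares. For the LBP part of the count,

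observed ratio = [N2 × (1 − s2)] / [N1 × (1 − s1)].

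- If s1 = s2, the ratio equals N2/N1. The level is too low but the relative change is right.
- If s changes, the ratio is wrong. With N1 = N2 and an assumed fall in the counted share (1 − s) from 40% to 30%, the ratio is 0.30 / 0.40 = 0.75, an apparent 25% drop with no change in visits.
- A shift the other way, from 30% to 40%, gives 0.40 / 0.30 = 1.33, an apparent 33% rise.

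If M54 is included, movement between M54 and the other categories stays inside the count and has no such effect.

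**The case against.** **Outside knowledge.** The article does not say what M54 contains. However, the plan itself chose ICD-10 as its counting rule, and reading the rule requires the code titles. No study result or outside estimate is used. This objection does not defeat the point.

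**Condensed article, or a slip for M40-M54.** Either may be true. But the article did not leave the code list to another document. It printed a specific range, and a slip in an extraction rule still needs correcting.

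**Same range in both periods.** This protects the relative change only while the M54 share is stable, as shown above. The article gives no assurance of that, and it reports a record-system change in one region. It does not say that this change alters coding, so the risk is possible, not demonstrated.

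**Limited consequence.** This stands. The count is neither the primary outcome nor given as the source of a secondary outcome. The visit counts in Table 7 come from patient questionnaires with no ICD range attached.

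Three stronger readings are tempting, and the article supports none of them:

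- *The count misses most LBP visits.* The figure of over 90% describes patients clinically, not the codes entered at appointments. Multiplying it by a guessed coding share only returns the guess.
- *The count is the denominator for imaging and secondary care.* Table 5 lists the three as separate measures, defines no ratio and does not attach the code range to the other two.
- *The education teaches clinicians to avoid structural labels and so pushes coding towards M54.* The Professional level section covers biopsychosocial explanation, harmful messages, imaging and the relevance of MRI findings. It never mentions diagnostic coding.

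**Conclusion.** Wrong as written, of minor severity. The printed range excludes M54, nothing in the article adds it or explains leaving it out, and this does not fit the population the article describes. The conclusion rests on the ordinary ICD-10 titles and on reading the row as a measure of LBP appointments, which its table and neighbouring row support.

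The share of LBP appointments lost may be large, but it depends on local coding, which the article does not report, so no figure can be given. The 25% drop and 33% rise in the working illustrate the mechanism under assumed shares and are not estimates for these regions.

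The effect is confined to one regional organisational measure and to whatever weight it carries in judging implementation. The PROMIS PF-20 primary outcome, the sample size of 340 and the patient-reported visit counts are untouched.

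**What to change.** In Table 5, change the range so that it includes M54: either M40-M54 or a stated LBP code list that contains M54. Suggested wording: *Number of physician appointments with an ICD-10 diagnosis in M40-M54, counted with the same code list before and after implementation in ESSOTE, EKSOTE and Rovaniemi.*

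If M54 was left out on purpose, state the reason and do not interpret the count as LBP appointments.

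A list restricted to lumbar codes, without categories such as M50, would match the condition more closely. It is optional: it goes beyond what this error requires, and any site-level restriction would need registers that record site, which the article does not address.

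The cost is a revised register extraction, including the period before implementation if that has already been drawn. The data are aggregate counts, so no patient contact is involved. EKSOTE may need more work, because earlier records may sit in the previous system.
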